**Factors other than therapeutic regimen known to affect 2-month culture-conversion**

##### Cavitation

Cavitation on chest radiograph is associated with a much lower rate of 2-month culture-conversion than is the case for patients with non-cavitary infiltrates (Table 8). This is true whether or not the initial sputum specimens were smear-positive or smear-negative for acid-fast bacilli. Therefore, randomization will be stratified by presence or absence of cavitation on the initial chest radiograph.

# Table 8. The effect of cavitation on 2-month culture conversion in TBTC Study 22 (TBTC, unpublished data)

*2-month culture conversion rate*

|  | *Cavitation* | *No cavitation* |
| --- | --- | --- |
| All HIV-negative patients | 70% (315/450) | 90.4% (356/394) |
| Only patients with initial smear-positivity | 66.6% (241/362) | 84.5% (169/200) |

##### HIV infection

A substantial proportion of patients enrolling in this trial will have HIV infection. Given the tremendous numbers of patients with HIV-related tuberculosis in the world, it is critical that any new treatment regimen be evaluated among HIV-infected persons. Although HIV infection was associated with a higher rate of 2-month culture conversion in TBTC Study 22[42], this difference did not retain significance after adjusting for the presence of cavitation, and other studies have not found a consistent association between HIV infection and 2-month culture-conversion rate (Table 9).

# Table 9. The effect of HIV infection on 2-month sputum culture conversion

*2-month culture conversion rate*

| *Study* | *HIV-positive* | *HIV-negative* |
| --- | --- | --- |
| Study 22 (TBTC, unpublished data) | 90.4% (47/52) | 79.4% (682/865) |
| Zaire [43] | 92.9% (223/240) | 92.1% (164/178) |
| Sterling (time to culture conversion) [44] | 77 days | 72 days |

INH resistance

Mycobacterial culture and drug susceptibility testing can require up to 8 weeks. Therefore, patients having drug-resistant isolates are likely to be enrolled in this trial and treated for most of the intensive phase of therapy prior to the receipt of the drug-susceptibility test results. The most common form of drug resistance in the United States, Canada, and Uganda is INH-resistance, with rates of 5-10% among patients without prior tuberculosis treatment. INH-resistance does not appear to have a substantial impact on sputum culture conversion (Table 10). However, INH-resistance appears to be associated with slightly higher rates of treatment failure and relapse, raising the possibility that absence of difference in 2-month sputum culture conversion rates may not indicate equivalence. In addition, current TB treatment guidelines suggest use of rifampin, pyrazinamide, plus ethambutol for individuals with INH-resistant isolates. Therefore, patients with INH-resistant isolates will be taken off of their assigned study regimen and treated using an individualized regimen at the discretion of the principal investigator. These patients will not be included in the analysis of sputum culture conversion.

**Table 10.** Effect of initial resistance to INH on outcomes of TB treatment [45]

| Outcome | INH-resistance | Drug-susceptible |
| --- | --- | --- |
| 2-month sputum culture conversion | 88% (132 / 150) | 89% (1123 / 1262) |
| Treatment failure | 0.6% (1 / 172) | 0.1% (2 / 3177) |
| Relapse | 9.0% (13 / 149) | 4.0% (123 / 2954) |

# The effect of laboratory techniques on the yield of sputum culture

A variety of culture systems are used to grow *M. tuberculosis*, and TBTC and the Uganda sites do not have a standardized culture system. No single culture technique has 100% sensitivity. However, as shown in Table 11, the use of a broth culture medium increases the yield of sputum culture by about 7%. Furthermore, the yield of using broth and solid media is consistently higher than using any one of these techniques alone. In a study using sputum culture conversion as the primary endpoint, it is important to standardize sputum culture techniques as much as possible. In this trial, all sites will be required to use both a licensed broth culture system and solid media for sputum cultures after enrollment. Reporting of results from both broth and solid media is required for each sputum specimen.

**Table 11.** The effect of culture technique on the yield of sputum mycobacterial cultures

| *Study* | *BACTEC 460* | *MGIT* | *BACTEC 9000* | *MB/BacT* | *Solid media* | *Difference between BACTEC 460 and solid media* |
| --- | --- | --- | --- | --- | --- | --- |
| Stager (n = 143)[46] | 89% |  |  |  | 80% | 9% |
| Wilson (n = 230) [47] | 92% |  |  |  | 86% | 6% |
| Idigoras (n = 315) [48] | 93% |  |  |  | 80% | 13% |
| Hanna (n = 130) [49] | 90% | 77% |  |  | 79% | 11% |
| Manterola (n = 100) [50] | 90% |  |  | 98% | 94% | -4% |
| Somoskovi (n = 55) [51] | 93% | 96% |  |  | 82% | 7% |
| Brunello (n = 115) [52] | 100% |  |  | 99% | 98% | 2% |
| Pfyffer (n = 247) [53] | 92% |  | 84% |  | 85% | 7% |
| Average | 92.4% | 86.5% | 84% | 98.5% | 85.8% | 6.6% |

Approximately 3-5% of sputum cultures for mycobacteria have bacterial or fungal overgrowth (despite decontamination procedures), making it impossible to determine whether there may have been mycobacteria present as well. To maximize the proportion of patients who can be analyzed for the primary endpoint, 2-month culture conversion, 2 sputum specimens will be collected at the completion of the four-drug phase of therapy.

# Risk factors for treatment failure and relapse

Large clinical trials, including TBTC Study 22, have identified consistent risk factors for poor outcomes from tuberculosis therapy (treatment failure or relapse). The most potent risk factors include the presence of cavitation on chest radiograph and 2-month sputum culture-positivity[42, 54, 55]. Patients with both of these factors had a particularly high rate of treatment failure or relapse (22% in TBTC Study 22) [42]. The consistency of the effect of 2-month culture conversion on risk of relapse has led to the recommendation that therapy be changed for such patients (ATS/IDSA/CDC guidelines for treatment of tuberculosis). The optimal management of patients at high risk for treatment failure or relapse will require additional study. The most promising management strategy is the extension of therapy. In a randomized trial of the treatment of silicotuberculosis, the extension of therapy by an additional 2 months (from 6 to 8 months) decreased the relapse rate from 20% to 2%[56]. In this trial patients with cavitation and 2-month culture positivity will be treated as recommended by the ATS/IDSA/CDC guidelines – an extension of therapy by 3 months.

- 1. Study Drugs

# Moxifloxacin

Moxifloxacin is a fluoroquinolone antibacterial, which is distinguished by a methoxy group at the C-8 position, and an S,S-configured diazabicyclononyl ring moiety at the C-7 position. The mechanism of action against *M. tuberculosis* is thought to be by inhibition of the DNA gyrase enzyme involved in DNA replication.

[figure not shown]

Moxifloxacin structure [Diagram obtained from package insert] [57]

##### Pharmacokinetics

[figure not shown]
Moxifloxacin is well absorbed, with a bioavailability of approximately 90% [58]. Pharmacokinetics are linear in the range of 50-800 mg single dose and up to 600 mg once daily dosing over 10 days[59]. Steady state is reached within 3 days[60]. The mean (+SD) maximum concentration (Cmax ) and AUC values at steady state with a 400 mg once-daily dosage regimen are 4.5+0.53 mcg/ml and 48+2.7 µg*h/ml, respectively[61]. Tmax is approximately 1-3 hours. The mean (+SD) plasma half-life is 12.1 + 3.1 hours. Trough plasma concentration at steady state (400 mg once daily) is 0.95 + 0.10 mcg/L. Co-administration with food may slightly prolong Tmax, and may reduce the Cmax by 16%; these effects are not believed to be clinically significant, and thus moxifloxacin can be administered with or without food. Administration with yogurt[62] or a high fat meal[63] did not significantly affect the AUC. However, concomitant administration with certain medications may substantially diminish the absorption of all fluoroquinolones (see below). Moxifloxacin is 50% bound to plasma proteins. It is widely distributed, with some tissue concentrations reported in excess of plasma levels[64].

Moxifloxacin is metabolized by glucuronide and sulfate conjugation. The cytochrome p450 enzyme system is not involved in the metabolism of moxifloxacin, nor is it affected by the drug. Specifically, moxifloxacin does not affect CYP3A4, CYP2D6, CYP2C9, CYP2C19, or CYP1A2. The sulfate conjugate (M1) accounts for 38% of the oral dose, and is excreted in feces; about 14% of an oral dose is converted to the glucuronide conjugate (M2), and is excreted in urine[65]. Peak plasma levels of M1 and M2 are <10% and about 40% those of the parent drug, respectively. Overall, about 45% of an oral dose is excreted as parent drug, and about 51% as known metabolites.

# Table 12. Moxifloxacin pharmacokinetics in special populations

| Population | Dose/Regimen | Findings |
| --- | --- | --- |
| Healthy elderly (16) [66] | Single 200-mg dose | AUC and Cmax similar in young and elderly males |
| Elderly (16) and young (18) males and females [66] | Elderly: single 200-mg dose  Young: single 400-mg dose | No gender differences when weight differences considered |
| Japanese males | Steady state | Similar to Caucasians |
| Renal insufficiency (24) [67] | Single dose | In patients with moderate and severe impairment, Cmax was reduced 21-22%; AUC increased 13%; AUC-M1 increased 1.7-fold; AUC-M2 increased 2.8-fold |
| Hepatic insufficiency (16: 6 Child Pugh Class A, & 10 Child Pugh Class B) | Single 400-mg dose | In class B patients, AUC of parent drug was unchanged; AUC-M1 increased 5.7-fold; AUC-M2 increased 1.5-fold; no data on Class C |
| Continuous ambulatory peritoneal dialysis (CAPD) or hemodialysis |  | Not studied |
| Pediatric |  | Not studied |

### Drug-drug interactions

Interaction studies have been performed with moxifloxacin and theophylline[68], warfarin, digoxin, probenecid[69], ranitidine, glyburide[70], iron[71], calcium supplements[72], sucralfate[73], and antacids[74]. Only a few clinically significant interactions have been described. All fluoroquinolones can bind to multivalent cations (esp. Fe+3, Al+3, and Mg+2, but not Ca+2], with resultant substantial (40-60%) decreases in absorption when taken concurrently. Moxifloxacin should not be administered at the same time as antacids containing magnesium and/or aluminum, sucralfate, antidiarrheals that contain kaolin, or iron and/or zinc containing medications or supplements.

Rifampin induces the activity of the phase II enzymes glucuronosyltransferase and sulphotransferase [75]. Interaction studies between rifampin and moxifloxacin have not been performed. However, because glucuronidation is a minor pathway in moxifloxacin metabolism (accounting for approximately 20% of total hepatic metabolism), a significant interaction between rifampin and moxifloxacin is unlikely.

Tolerability

As a class, fluoroquinolones are considered to be safe and relatively free of serious adverse effects[76]. The safety and efficacy of moxifloxacin for the treatment of community acquired bacterial infections has been extensively studied, and the drug is approved in the U.S. as a 10-day course of treatment for upper and lower respiratory tract infections.

In the usual daily doses of 400 mg/day, moxifloxacin is well tolerated. Expected minor adverse events have occurred with a frequency similar to that for other fluoroquinolones in similar populations. Gastrointestinal adverse effects are the most common, and they include nausea (7%), diarrhea (6%), dizziness (3%), abdominal pain (2%), vomiting (2%), dyspepsia (1%), and taste perversion (1%). There are no current reports of hepatitis, although abnormal liver function tests have been noted in 1% of patients.

Of note, fluoroquinolones are generally used short-term for acute conditions. However, fluoroquinolones have been found to be safe and effective in long term use for chronic infections such as osteomyelitis, prostatitis, or chronic urinary tract infection, or skin and skin structure infections[76, 77]. In addition, Valerio et al. found that the combination of moxifloxacin, isoniazid, and rifampin given for 6 months was well tolerated[32].

## Cardiotoxicity

The QT interval is the electrocardiographic measurement that describes the period between onset of ventricular depolarization and the end of the repolarization process. Prolongation of this interval is thought to be associated with an increased risk of ventricular tachy-arrhythmias. Moxifloxacin causes a mild prolongation of the corrected QT (QTc) interval[78]. The mean effect on QTc interval in 787 patients in Phase 3 clinical trials was 6 + 26 milliseconds, but no morbidity or mortality was attributable to QTc prolongation. In a review of over 6,000 patients treated with moxifloxacin, there were no reports of changes in the frequency of QTc prolongation[79]. In over 10 million patients treated with moxifloxacin there has been no evidence for an increased incidence of ventricular arrhythmia when compared to the overall population. No ventricular arrhythmias attributable to QTc prolongation have been reported to date. Finally, the incidence of sudden death and syncope, both markers for sudden cardiac events, is not increased when compared to the incidence on the general population. For these reasons, electrocardiographic monitoring is no longer recommended for clinical trials involving moxifloxacin.

In this study, moxifloxacin will not be used among patients with a known history of prolongation of the QT interval, patients with uncorrected hypokalemia and patients receiving class Ia (e.g. quinidine, procainamide) or class III (e.g. amiodarone, sotalol) antiarrythmic agents, due to the lack of clinical experience with the drug in these patient populations (see Exclusion criteria). Pharmacokinetic studies between moxifloxacin and other drugs that prolong the QT interval such as cisapride, erythromycin, antipsychotics and tricyclic antidepressants have not been performed. An additive effect of moxifloxacin and these drugs cannot be excluded, therefore moxifloxacin should be used with caution when given concurrently with these drugs.

Phototoxicity/Photosensitivity

Photosensitivity is defined as a non-immunological, light-activated irritation that occurs following exposure to a photoactive chemical. This is an infrequent adverse event of most fluoroquinolones. Moxifloxacin, has been found to have no negative phototoxic effects and in some patients was shown to be photoprotective at specific wavelengths.

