### Exclusion criteria

1. Breast-feeding
2. Known intolerance to any of the study drugs
3. Known allergy to any fluoroquinolone antibiotic
4. Concomitant disorders or conditions for which moxifloxacin, isoniazid, rifampin, pyrazinamide, or ethambutol are contraindicated. These include severe hepatic damage, acute liver disease of any cause, and acute uncontrolled gout.
5. Current or planned therapy during the intensive phase of tuberculosis treatment using drugs having unacceptable interactions with rifampin (rifabutin can be substituted for rifampin during the continuation phase of therapy)
6. Current or planned antiretroviral therapy during the intensive phase of tuberculosis treatment
7. History of prolonged QT syndrome or current or planned therapy with quinidine, procainamide, amiodarone, sotalol, disopyramide, ziprasidone, or terfenadine during the intensive phase of tuberculosis treatment.
8. Pulmonary silicosis
9. Central nervous system TB

Primary endpoints

1. The proportion of patients having a negative sputum culture at 2 months of therapy
2. The proportion of patients who discontinue assigned study therapy for any reason during the first 2 months

Study Management

Patients will have study visits every two weeks during the first 2 months of therapy. At each study visit, there will be a clinical assessment for toxicity and a sputum specimen will be obtained for smear and culture (two sputum specimens will be obtained after 8-weeks). Mycobacterial cultures must include an approved broth culture system, supplemented by at least one solid medium. Patients who are unable to produce an expectorated sputum specimen at weeks 2, 4, 6, or 8 will have sputum induction.

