- Serum amino aspartate transferase (AST) activity ≤ 3 times the upper limit of normal
- Serum total bilirubin level ≤ 2.5 times the upper limit of normal
- Serum creatinine level ≤ 2 times the upper limit of normal
- Complete blood count with hemoglobin level of at least 7.0 g/dL
- Complete blood count with platelet count of at least 50,000/mm3
- Serum potassium ≥ 3.5 meq/L
- Negative pregnancy test (women of childbearing potential)
  - 1. Exclusion Criteria

1. Breast-feeding
2. Known intolerance to any of the study drugs
3. Known allergy to any fluoroquinolone antibiotic
4. Concomitant disorders or conditions for which moxifloxacin (MXF), isoniazid (INH), rifampin (RIF), pyrazinamide (PZA), or ethambutol (EMB) are contraindicated. These include severe hepatic damage, acute liver disease of any cause, and acute uncontrolled gouty arthritis.
5. Current or planned therapy during the intensive phase of therapy using drugs having unacceptable interactions with rifampin (rifabutin can be substituted for rifampin during the continuation phase of therapy)
6. Current or planned antiretroviral therapy during the intensive phase of therapy
7. History of prolonged QT syndrome or current or planned therapy with quinidine, procainamide, amiodarone, sotalol, disopyramide, ziprasidone, or terfenadine during the intensive phase of therapy.
8. Pulmonary silicosis
9. Central nervous system TB
10. **STUDY PLAN**
    1. Study Procedures
       1. Screening Visit

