Moxifloxacin does have the potential to prolong the QT interval, a class property of the fluoroquinolones. Quinidine, procainamide, sotalol, amiodarone, disopyramide, terfenadine, and ziprasidone are contraindicated for use with moxifloxacin. If a patient requires therapy with one of these agents, they will be taken off blinded study medication and alternate TB treatment will be prescribed by the principal investigator. Other drugs that may have an effect on QT interval should be used with caution during blinded study treatment: cisapride, erythromycin, clarithromycin, perphenazine, phenothiazines, and tricyclic antidepressants.

Isoniazid decreases the clearance of some medications that are metabolized in the liver. Patients who take isoniazid and require the following medications will have appropriate serum drug levels measured to prevent toxicity: carbamazepine, phenytoin, and theophylline. Antacids that contain aluminum and/or magnesium and antidiarrheals that contain kaolin can decrease isoniazid, ethambutol, and moxifloxacin absorption. Study patients requiring the use of antacids containing aluminum and/or magnesium, sucralfate, antidiarrheals that contain kaolin, or iron and/or zinc-containing medications or supplements will need to take their study drugs at least 4 hours before or 8 hours after ingesting these products to avoid impaired absorption of study drugs.

Rifampin induces a number of hepatic enzyme systems that are active in the metabolism of many drugs. The most common site of rifampin-related interactions is the cytochrome CYP450 enzyme system. Suggestions for the management of rifampin-related drug interactions are given in Appendix C. A prominent drug interaction of rifampin is that involving hormonal contraceptives. Women of childbearing potential (i.e., not surgically sterilized or postmenopausal for less than 1 year) will be advised to use one or more of the following contraceptive methods: intrauterine device; barrier methods including the diaphragm or cervical cap (each used with spermicidal foam or jelly), condom, and sponge; or abstinence.

Ethanol can exacerbate the potential hepatotoxicity of isoniazid, rifampin, and pyrazinamide. Participants will be urged to abstain from alcohol while on study phase therapy.

- 1. HIV management

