| Neutrophils/  granulocytes  (ANC/AGC) | WNL | >1.5 - <2.0 x 10/L  >1500  <2000/mm 3 | >1.0 - <1.5 x  109 /L  >1000<  1500/mm 3 | >0.5 - <1.0 x  109 /L  >500  <1000/mm 3 | <0.5 x 10 9 /L  <500/mm 3 |
| Platelets | WNL | <LLN - 75.0 x  10 9 /L  <LLN  75,000/mm 3 | >50.0 - <75.0 x  10 9 /L  >50,000 -  <75,000/mm 3 | >10.0 - <50.0 x  10 9 /L  >10,000 -  <50,000/mm 3 | <10.0 x 10 9 /L  <10,000/mm 3 |
| Blood/Bone  Marrow - Other  (Specify,_____  ____) | none | mild | moderate | severe | life-threatening or  disabling |

| CARDIOVASCULAR (ARRHYTHMIA) | | | | | |
| --- | --- | --- | --- | --- | --- |
| Conduction  abnormality/  Atrioventricular heart block | none | asymptomatic, not  requiring  treatment  (e.g., Mobitz type  I second-degree  AV block,  Wenckebach) | symptomatic,  but not  requiring  treatment | symptomatic  And requiring  treatment  (e.g., Mobitz type II,second-degree AV  block, third  degree AV  block) | life-threatening  (e.g., arrhythmia  associated  with CHF,  hypotension,  syncope, shock) |
| Nodal/junctional  arrhythmia/  dysrhythmia | none | asymptomatic, not  requiring  treatment | symptomatic,  but not  requiring treatment | symptomatic  and requiring  treatment | life-threatening  (e.g.,arrhythmia  associated  with CHF, hypotension,  syncope, shock) |
| Palpitations  Note: Grade  palpitations only  in the absence of  a documented  arrhythmia. | none | present | - | - | - |
| Prolonged QTc  interval  (QTc >0.48 seconds) | none | asymptomatic, not  requiring  treatment | symptomatic,  but not  requiring  treatment | symptomatic  and requiring  treatment | life-threatening  (e.g.,arrhythmia  associated with  CHF,  hypotension,  syncope, shock) |
| Sinus bradycardia | none | asymptomatic, not  requiring  treatment | symptomatic,  but not  requiring  treatment | symptomatic  and requiring  treatment | life-threatening  (e.g.,arrhythmia\  associated  with CHF,  hypotension,  syncope, shock) |
| Sinus tachycardia | none | asymptomatic, not  requiring  treatment | symptomatic,  but not  requiring treatment | symptomatic  and requiring  treatment of  underlying  cause | - |

| Supraventricular  arrhythmias  (SVT/atrial  fibrillation/  flutter) | none | asymptomatic, not  requiring  treatment | symptomatic,  but not  requiring  treatment | symptomatic  and requiring  treatment | life-threatening  (e.g., arrhythmia  associated  with CHF, hypotension,  syncope, shock) |
| --- | --- | --- | --- | --- | --- |

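### The Cardiotoxicity text bars moxifloxacin with any class Ia or class III antiarrhythmic, but exclusion 7 and the section 5.10 stopping rule cover only seven named drugs

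*Protocol*

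**What the plan says.** Four places in the Protocol bear on this.

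- **2.2 Study Drugs, Moxifloxacin, Cardiotoxicity.** For this study, "moxifloxacin will not be used among patients with a known history of prolongation of the QT interval". The same sentence adds patients with uncorrected hypokalemia and "patients receiving class Ia (e.g. quinidine, procainamide) or class III (e.g. amiodarone, sotalol) antiarrythmic agents". The reason given is lack of clinical experience in these groups, and the sentence points to the exclusion criteria. The paragraph then asks for caution with other QT-prolonging drugs, antipsychotics among them.
- **3.8.2 Exclusion Criteria, item 7.** This excludes "History of prolonged QT syndrome or current or planned therapy with quinidine, procainamide, amiodarone, sotalol, disopyramide, ziprasidone, or terfenadine" in the intensive phase.
- **Synopsis, Exclusion criteria, item 7.** The list is the same, ending "amiodarone, sotalol, disopyramide, ziprasidone, or terfenadine during the intensive phase of tuberculosis treatment".
- **5.10 Concomitant medications during study phase.** "Quinidine, procainamide, sotalol, amiodarone, disopyramide, terfenadine, and ziprasidone are contraindicated for use with moxifloxacin". The action follows: "If a patient requires therapy with one of these agents, they will be taken off blinded study medication". For everything else, "Other drugs that may have an effect on QT interval should be used with caution during blinded study treatment", followed by six entries, none of them an antiarrhythmic.

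**The concern.** The Cardiotoxicity text states a rule for the trial and presents the exclusion criteria as the place where it is enforced. Those criteria, and the matching stopping rule, do not contain the rule as stated: two drug classes have become a list of names.

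The form matters because the trial is double-blind. A site does not know who is receiving moxifloxacin, so a rule that the drug will not be used in certain patients can be kept only by not enrolling them or by taking them off blinded drug. The synopsis also says that no electrocardiographic monitoring will be done. Control of QT risk therefore rests on history, medication review and these lists. An agent that belongs to a barred class but is not listed drops from prohibited to caution at most.

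**Working it through.** No plan figure is involved and no formula applies. The check sets the texts side by side.

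| Item | Cardiotoxicity (2.2) | Exclusion 7 (synopsis, 3.8.2) | 5.10 |
|---|---|---|---|
| Class Ia and III antiarrhythmics | Both classes, four drugs as examples | Seven named drugs, no class wording | Same seven; stopping tied to these |
| Timing | Patients receiving the drug | Current or planned therapy | Need arising on blinded drug |
| Ziprasidone, terfenadine | Not barred by name | Barred | Barred |
| QT history | Known prolongation of the interval | Prolonged QT syndrome | No rule (a co-medication section) |
| Hypokalemia | Uncorrected hypokalemia | Not here; inclusion limit of 3.5 meq/L or more | No rule |

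**Step 1, the drugs.** The Cardiotoxicity text names four: quinidine, procainamide, amiodarone and sotalol. All 4 of 4 are on both lists. The lists hold 7, so 7 − 4 = 3 are added: disopyramide, ziprasidone and terfenadine.

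**Step 2, an unlisted class Ia or III agent.** The Cardiotoxicity text bars it. Exclusion 7 does not reach it, having neither class wording nor an open-ended phrase. The 5.10 stopping rule does not reach it either, because the rule is confined to the listed agents. It could fall under the 5.10 caution sentence, but that sentence does not name it. Exclusion 4 concerns disorders and conditions that contraindicate a study drug, not co-medication.

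**Step 3, the other direction.** Exclusion 7 is wider in two respects: it covers planned therapy, and it bars ziprasidone and terfenadine. The Cardiotoxicity text leaves antipsychotics under caution. Taking ziprasidone to be an antipsychotic (general pharmacology, not stated in the Protocol), that text and the lists disagree on it.

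**Step 4, QT history.** The terms differ, but the second may simply be loose wording for the first. Appendix E treats prolonged QTc as a measured finding ("QTc >0.48 seconds") that can be asymptomatic. It is a toxicity-grading table, however, and does not define the eligibility term.

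**Step 5, hypokalemia.** The potassium limit carries this group over at entry. Appendix D schedules potassium at screening only, so it is not enforced afterwards.

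**Step 6, size.** Beyond its four examples, the Protocol identifies no agent as class Ia or III. A count of affected patients cannot be derived.

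**The case against.** The strongest reply is that the Cardiotoxicity text is background and defers to the exclusion criteria, which decide enrolment. On this view exclusion 7 is the working form of the class statement: it contains every example and adds three drugs, and the synopsis, 3.8.2 and 5.10 agree with one another. A named list is also easier for sites to apply uniformly than a class. Further cover comes from medication review at each intensive-phase visit and from the investigator's freedom to hold or stop therapy (5.7, 5.8).

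Much of this stands. The operative sections are consistent with one another, the cover is real though partial, and nothing shows that any patient would be affected. But the background sentence speaks of this study and sends the reader to criteria that say something narrower, so one of the two needs changing. Discretion and caution are also weaker than a prohibition. Class wording with the drugs kept as examples gives sites both the rule and the names.

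Two stronger readings are tempting. A reader might infer that the phrase about a QT syndrome lets in patients with known QT prolongation. The documents do not support that: the phrase is plausibly a synonym, Appendix E does not settle it, and exclusion 4 could be read to cover such a condition. A reader might also infer that the criteria are looser than the background throughout. They are not, as Step 3 shows.

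**Conclusion.** The point holds for the antiarrhythmic classes. As written, an unlisted class Ia or III agent does not exclude a patient and does not stop blinded drug, although the Cardiotoxicity text says moxifloxacin will not be used with it. This is a minor alignment of safety wording that bears on who may be enrolled or kept on blinded drug. The number of patients concerned cannot be derived and may be zero. Efficacy, power and alpha are unaffected.

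The conclusion rests on reading the Cardiotoxicity sentence as a rule for the trial and its drugs as examples, which is what its wording says. The QT-history phrase is a secondary clarification only.

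**What to change.** 1. In exclusion 7 (synopsis and 3.8.2) and in the 5.10 contraindication sentence, replace the drug list with: *any class Ia or class III antiarrhythmic (e.g. quinidine, procainamide, disopyramide, amiodarone, sotalol), ziprasidone, or terfenadine*. Keep the current-or-planned wording in exclusion 7. The 5.10 stopping rule then follows without further change. Disopyramide remains named, so its status does not depend on how a site classifies it.
2. As a secondary clarification, change the history phrase in exclusion 7 to *known history of QT-interval prolongation*, which is probably what was meant.
3. In the Cardiotoxicity text, note that ziprasidone is barred rather than subject to caution.

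No new procedure is needed: screening already asks about medical history and medications, and each intensive-phase visit asks about medications again. The edits touch eligibility and a stopping rule, so they need ethics approval under the Protocol's section on institutional review board involvement, and the consortium has sites in six countries. They are best carried in an amendment made for other reasons as well. The downside is possibly a very few more exclusions or stops. A patient stopped in the first two months would count in the discontinuation endpoint, under the same blinded rule in either arm.
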